## Appendix C

### List of possible adverse events caused by varenicline and NRT lozenges based on severity:

| Varenicline adverse events                                                                                                                                                                                                                                                                                                                                                                                                                                                                                                                                                                                                                                                                                                                                                                                                                                                                                                                                                                                                                 |                                                                                                                                                                                                                             |                                                                                                                                                                                                                                                                              |
|--------------------------------------------------------------------------------------------------------------------------------------------------------------------------------------------------------------------------------------------------------------------------------------------------------------------------------------------------------------------------------------------------------------------------------------------------------------------------------------------------------------------------------------------------------------------------------------------------------------------------------------------------------------------------------------------------------------------------------------------------------------------------------------------------------------------------------------------------------------------------------------------------------------------------------------------------------------------------------------------------------------------------------------------|-----------------------------------------------------------------------------------------------------------------------------------------------------------------------------------------------------------------------------|------------------------------------------------------------------------------------------------------------------------------------------------------------------------------------------------------------------------------------------------------------------------------|
| Common (rate $\geq 1\%$ )                                                                                                                                                                                                                                                                                                                                                                                                                                                                                                                                                                                                                                                                                                                                                                                                                                                                                                                                                                                                                  | Uncommon ( $\geq 1/1,000$ , $< 1/100$ )                                                                                                                                                                                     | Rare but serious ( $\geq 1/10,000$ to $< 1/1,000$ )                                                                                                                                                                                                                          |
| 
 
- nausea
 
- vomiting
 
- indigestion
 
- constipation
 
- abdominal pain
 
- increased appetite
 
- weight gain
 
- headache
 
- insomnia
 
- abnormal dreams
 
                                                                                                                                                                                                                                                                                                                                                                                                                                                                                                                                                                                                                                                                                                                                                            | 
 
- mood swings
 
- restlessness
 
- muscle spasms
 
- dry mouth
 
- increased heart rate
 
- tremor
 
- increased blood pressure
 
 | 
 
- thoughts of self-harm
 
- changes in mood or behaviour
 
- rash or itchy swelling on skin
 
- breathing problems
 
- swelling of the face, lips, mouth, tongue, throat
 
- chest pain
 
 |
| 
For some people stopping smoking with or without the aid of treatment has been linked to changes in behaviour, mood or thinking e.g. developing suicidal thoughts or anxiety. Some people had these symptoms when they began taking varenicline (Champix), and others developed them after several weeks of treatment or after stopping. It is not known whether these changes are related to Champix, as mood changes can also occur as a result of stopping smoking.
 
Drinking alcohol while taking varenicline can increase the effects of alcohol. It may also increase your risk of experiencing changes to your behaviour, thinking or mood and there have also been reports of increased feelings of being drunk while taking varenicline. Should you choose to agree to participate in this study, we recommend that you avoid drinking alcohol or be careful if drinking alcohol while taking this medicine and consult your Research Assistant or GP if you notice any changes in your behaviour, mood or thinking.
 |                                                                                                                                                                                                                             |                                                                                                                                                                                                                                                                              |

| NRT lozenges adverse events                                                                         |                                                                                                                                                                                                                    |                                                                                                                                                                                                                        |
|-----------------------------------------------------------------------------------------------------|--------------------------------------------------------------------------------------------------------------------------------------------------------------------------------------------------------------------|------------------------------------------------------------------------------------------------------------------------------------------------------------------------------------------------------------------------|
| Very Common ( $> 1/10$ )                                                                            | Common ( $> 1/100$ ; $< 1/10$ )                                                                                                                                                                                    | Uncommon ( $> 1/1000$ ; $< 1/100$ )                                                                                                                                                                                    |
| 
 
- nausea
 
- hiccups
 
- flatulence
 
 | 
 
- insomnia
 
- dizziness
 
- headache
 
- vomiting
 
- constipation
 
- heartburn
 
- indigestion
 
- dry mouth
 
 | 
 
- excessive thirst
 
- lethargy
 
- sore lips
 
- anxiety
 
- gastroesophageal reflux
 
- shortness of breath
 
- migraine
 
 |

## Appendix D

### Study flow diagram:

[figure not shown]

703  
704  
705

[figure not shown]

#### Aim and Objectives

This study aimed to evaluate the effectiveness and safety of the combination of varenicline and NRT lozenges at assisting achievement of abstinence amongst heavy smokers admitted to six ‘smoke-free’ public hospitals in Australia.

The primary objective of the study was to compare biochemically-verified continuous abstinence in hospitalised smokers treated using varenicline plus NRT lozenge versus varenicline monotherapy.

#### Sample size

Continuous abstinence rates at 52 weeks in clinical trials of varenicline were 22.5% for varenicline and 8.3% for placebo. To demonstrate an absolute difference of 15% in prolonged abstinence rate between study arms (estimate based on abstinence rates in varenicline-NRT trials) 6 at the 5% level of significance with 80% power, 160 subjects per arm were needed. A total of 320 participants were recruited from the five hospitals, i.e., 64 subjects from each hospital, 32 each in varenicline monotherapy and varenicline + NRT lozenges arms.

### Statistical Analyses

Analyses will be performed using SPSS or Stata version 17 (StataCorp, TX, USA). Baseline characteristics of both groups will be summarised and differences between groups will be reported. Continuous variables will be initially assessed for normality and expressed as mean and standard deviation (SD) or medians and inter-quartile ranges [IQR] as appropriate. Categorical variables will be summarized using frequency counts and percentages.

**Table 1: Baseline characteristics of participants (n = 320)**

| Variables                                      | Intervention
n = 160 (%) | Control
n = 160 (%) | P-value |
|------------------------------------------------|-----------------------------|------------------------|----------------|
| Age in years, mean (<math>\pm</math>SD) |                             |                        |                |
| Male                                    |                             |                        |                |
| Born in Australia                       |                             |                        |                |
| Mainly spoke English at home            |                             |                        |                |
| Highest education                       |                             |                        |                |
| No formal schooling/Primary school or below    |                             |                        |                |
| High school                                    |                             |                        |                |
| Technical/further education                    |                             |                        |                |
| University education/postgraduate              |                             |                        |                |

|                                                                                                                                                                                                                                                                                                                                                               |  |  |  |
|---------------------------------------------------------------------------------------------------------------------------------------------------------------------------------------------------------------------------------------------------------------------------------------------------------------------------------------------------------------|--|--|--|
| Employment status*, Unemployed                                                                                                                                                                                                                                                                                                                         |  |  |  |
| Prior hospitalisation ≤6 months ago, Yes                                                                                                                                                                                                                                                                                                               |  |  |  |
| Depression (PHQ-9)                                                                                                                                                                                                                                                                                                                                     |  |  |  |
| Minimal depression (score 1-4)                                                                                                                                                                                                                                                                                                                                |  |  |  |
| Mild depression (score 5-9)                                                                                                                                                                                                                                                                                                                                   |  |  |  |
| Moderate depression (score 10-14)                                                                                                                                                                                                                                                                                                                             |  |  |  |
| Moderately severe depression (score 15-19)                                                                                                                                                                                                                                                                                                                    |  |  |  |
| Severe depression (score 20-27)                                                                                                                                                                                                                                                                                                                               |  |  |  |
| Reason for hospital admission                                                                                                                                                                                                                                                                                                                          |  |  |  |
| Cardiovascular disorder                                                                                                                                                                                                                                                                                                                                       |  |  |  |
| Respiratory disorder                                                                                                                                                                                                                                                                                                                                          |  |  |  |
| Digestive system disorder                                                                                                                                                                                                                                                                                                                                     |  |  |  |
| Musculoskeletal disorder                                                                                                                                                                                                                                                                                                                                      |  |  |  |
| Other †                                                                                                                                                                                                                                                                                                                                            |  |  |  |
| Age at smoking onset, mean (±SD), years                                                                                                                                                                                                                                                                                                                |  |  |  |
| Number of years of smoking, median (IQR)                                                                                                                                                                                                                                                                                                               |  |  |  |
| Heaviness of smoking index                                                                                                                                                                                                                                                                                                                             |  |  |  |
| Low nicotine dependence (score 0-2)                                                                                                                                                                                                                                                                                                                           |  |  |  |
| Moderate nicotine dependence (score 3-4)                                                                                                                                                                                                                                                                                                                      |  |  |  |
| High nicotine dependence (score 5-6)                                                                                                                                                                                                                                                                                                                          |  |  |  |
| Motivation to quit, median [IQR]                                                                                                                                                                                                                                                                                                                       |  |  |  |
| Confidence to quit, median [IQR]                                                                                                                                                                                                                                                                                                                       |  |  |  |
| Tried quitting at least once in the last 12 months, n (%)                                                                                                                                                                                                                                                                                              |  |  |  |
| Number of quit attempts in the last 12 months, median [IQR]                                                                                                                                                                                                                                                                                            |  |  |  |
| 
*Employed: full-time, part-time or casual; Unemployed: student, unemployed, home-duties, disabled, unable to work, retired/pensioner
 
†Other reasons for hospital admission include: conditions of the skin and soft tissues, reproductive, lymphatic, endocrine, urinary or nervous systems
 
PHQ-9: Patient Health Questionnaire-9
 |  |  |  |

819

820 The effectiveness analyses will be by intention to treat (ITT) and participants lost to follow-  
821 up will be regarded as smokers. Deceased participants will be excluded from analyses.

822 Abstinence outcomes (primary and secondary) at 3, 6 and 12 months will be estimated in  
823 each treatment arm. Logistic regression models (unadjusted) will be used to examine the  
824 efficacy of intervention on the primary and secondary abstinence outcomes at each follow-  
825 up visit, after testing homogeneity between hospitals using a random effects meta-analysis.  
826 In the event of heterogeneity, generalised estimating equation models incorporating  
827 clustering by hospital will be fitted.

828

829

830  
831  
832  
833  
834  
835  
836  
837  
838  
839  
840  
841  
842  
843  
844

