(1:1) using a randomisation scheme generated using a computer-generated list. Random block sizes of two and four will be used to reduce the predictability of treatment allocation. Each site will be provided with 64 envelopes containing the group allocation. The clinical trials pharmacist will open the envelopes in a sequential manner when a participant is recruited. The pharmacist will then dispense the study medicines as stated in the envelope ([varenicline and NRT lozenges] or [varenicline and placebo lozenges]) and hand these to the RA along with the envelope. The RA will then hand the medicine to the participant and provide detailed counselling. Participants will not be told whether they are receiving NRT or placebo lozenges.

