## 4. Statistical Considerations

### 4.1 Sample Size

To show a difference of 15% in continuous abstinence between study arms (based on continuous abstinence rate of 23% in varenicline trials) at the 5% level of significance with 80% power, we will need 160 subjects per arm. i.e. 320 participants in total from the six hospitals, , 160 in each of the study arms. The primary analysis will be intention to treat (ITT) and lost to follow-up participants will be regarded as smokers.

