### 4.2 Data Analysis

Data will be stored in a suitable database (e.g. REDCap™, ACCESS™) and exported for analysis in Statistical Package for Social Sciences (SPSS) (version 23.0; IBM, Armonk, NY) and Stata (ver 15, StataCorp, College Station, TX). As recommended by the Russell Standard, all randomised patients will be accounted for in the intention to treat (ITT) analysis. Participants with missing outcomes at follow-up or whose self-reported abstinence was not biochemically validated will be considered as smokers. Sensitivity analyses using multiple imputation methods will also be carried out. Deceased participants will be excluded from

analyses. In a supportive analysis of the primary efficacy endpoint, an analysis will also be conducted on the per protocol set, which excludes patients with any major protocol deviations.

Logistic regression analyses will be used to examine the efficacy of intervention on the primary outcome, after testing homogeneity between hospitals using a random effects meta-analysis. In the event of heterogeneity, a more robust model incorporating clustering by hospital will be fitted. The effect of intervention on continuous abstinence at 6 months will be tested in pre-specified subgroups (per hospital, nicotine dependence, highly motivated versus moderately motivated smokers and men versus women) using models fitted for each subgroup containing main effects for intervention and subgroup and an interaction between them. Statistical significance will be considered at a two-sided p value of 0.05.

All randomised participants who take at least one dose of the treatment medications will be included in the safety analysis. A chi-squared test will be done to compare the frequency of treatment withdrawal between the treatment and comparator arms. The number of participants discontinuing treatment prematurely for any reason will be summarised by treatment group and by reasons for discontinuation.

The incidence of all suspected adverse events will be summarised by treatment group under the following categories: type, severity, action taken and outcome. Severity of adverse events will be reported using the CTEAE grading scale (v5.0). The causality of the adverse events will be determined using the Noranjo algorithm.

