**Table 2: Smoking abstinence rates by treatment groups from 2 weeks to 3, 6 and 12 months**

| Outcome                                         | Intervention
n (%) | Control
n (%) | P-value | Odds
ratio
(95%
CI) | Adjusted
odds ratio
(95%CI) |
|-------------------------------------------------|-----------------------|------------------|----------------|------------------------------|-----------------------------------|
| Smoking abstinence at 3-months           |                       |                  |                |                              |                                   |
| Self-reported prolonged abstinence              |                       |                  |                |                              |                                   |
| Self-reported 7-day point prevalence abstinence |                       |                  |                |                              |                                   |
| Smoking abstinence at 6-months           |                       |                  |                |                              |                                   |
| Biochemically verified prolonged abstinence     |                       |                  |                |                              |                                   |
| Self-reported prolonged abstinence              |                       |                  |                |                              |                                   |
| Self-reported 7-day point prevalence abstinence |                       |                  |                |                              |                                   |
| Smoking abstinence at 12-months          |                       |                  |                |                              |                                   |
| Biochemically verified prolonged abstinence     |                       |                  |                |                              |                                   |
| Self-reported prolonged abstinence              |                       |                  |                |                              |                                   |
| Self-reported 7-day point prevalence abstinence |                       |                  |                |                              |                                   |

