Deceased participants at each time-point will be excluded from those specific analyses. All analyses will be adjusted for baseline HSI score.

HSI and PHQ-9 score differences from baseline to 3, 6 and 12 months will be compared between the treatment groups using Mann-Whitney U tests.

**Table 3: Heaviness of Smoking Index and Patient Health Questionnaire-9 score differences from baseline to 3, 6 and 12 months**

| Outcome          | Baseline     |         | 3-months     |         | 6-months     |         | 12-months    |         |
|------------------|--------------|---------|--------------|---------|--------------|---------|--------------|---------|
|                  | Intervention | Control | Intervention | Control | Intervention | Control | Intervention | Control |
| HSI score |              |         |              |         |              |         |              |         |
| HSI score | ----         | ----    |              |         |              |         |              |         |

|                                                   |      |      |  |  |  |  |  |  |
|---------------------------------------------------|------|------|--|--|--|--|--|--|
| (% participants showing improvement) † |      |      |  |  |  |  |  |  |
| PHQ-9 score                                       |      |      |  |  |  |  |  |  |
| PHQ-9 score (% participants showing improvement)  | ---- | ---- |  |  |  |  |  |  |

860 \*Indicates significant differences ( $p < 0.05$ ) between the intervention and control groups. †Follow-up score  
861 lower than baseline score indicates improvement

862  
863  
864  
865  
866  
867

868 A data safety and monitoring board (DSMB) provided oversight of adverse event data on a  
869 periodic basis. For the primary safety outcome, the proportion of reported adverse events  
870 occurring between treatment initiation and over 12-month follow-up will be compared  
871 between the treatment groups using a  $\chi^2$  test or Mann-Whitney U tests, as appropriate.

872 **Table 4: Adverse events experienced by treatment group**

| Outcome                                                              | Intervention | Control | P-value |
|----------------------------------------------------------------------|--------------|---------|----------------|
| Adverse events experienced at week 1 * , n (%)            |              |         |                |

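### The SAP describes the primary abstinence model as both unadjusted and HSI-adjusted, and Table 2 has one P-value column tied to neither odds ratio

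*Combined protocol and SAP*

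**What the plan says.** - **SAP, Statistical Analyses, text between Tables 1 and 2.** The model sentence opens "Logistic regression models (unadjusted) will be used to examine the" and covers both the primary and the secondary abstinence outcomes at each follow-up. If hospitals prove heterogeneous, it moves to generalised estimating equations (GEE) clustered by hospital, with no word on covariates.
- **SAP, note under Table 2.** "All analyses will be adjusted for baseline HSI score".
- **SAP, Table 2 ("Smoking abstinence rates by treatment groups from 2 weeks to 3, 6 and 12 months").** The columns are counts by arm, one P-value, an odds ratio with 95% CI, and an adjusted odds ratio with 95% CI. Nothing says which model supplies the P-value.
- **SAP, Table 6 (per protocol).** There is one odds ratio column, not labelled adjusted or unadjusted. Its note repeats the sentence on deceased participants but not the one on HSI.
- **Protocol, section 4.2.** Logistic regression is specified for the primary outcome and no covariate is named. "Statistical significance will be considered at a two-sided p value of 0.05".
- **Protocol, section 4.1.** "To show a difference of 15% in continuous abstinence between study arms (based on continuous abstinence rate of 23% in varenicline trials") and, "at the 5% level of significance with 80% power, we will need 160 subjects per arm".

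**The concern.** The two SAP statements cannot both be followed for the primary outcome. Neither model is called primary, supportive or sensitivity, and the protocol does not settle the matter. The single P-value could come from either model, so either could be defended as pre-specified once the results are known.

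Three further details are open. The GEE fallback does not say whether it is adjusted, so up to four models (logistic or GEE, each with or without HSI) could supply the primary p-value. The form of HSI is not fixed: the note speaks of a score, while Table 1 uses three categories. And the two odds ratio columns estimate different quantities, because odds ratios are not collapsible: the unadjusted one is marginal, the other conditional on HSI.

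At stake is a uniquely defined primary test, and the type I error if the choice is made after the data are seen.

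**Working it through.** **Step 1: reproduce the plan's sample size.** Inputs from protocol 4.1 and 4.2: p1 = 0.23, p2 = 0.23 + 0.15 = 0.38, two-sided alpha 0.05, power 80%.

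n0 = [z(0.975)·√(2·p̄·(1−p̄)) + z(0.80)·√(p1(1−p1) + p2(1−p2))]² / (p2−p1)²

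With p̄ = 0.305: n0 = [1.960·√0.42395 + 0.8416·√0.4127]² / 0.0225 = (1.2762 + 0.5407)² / 0.0225 = 146.7, so 147.

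Continuity correction: n = (n0/4)·[1 + √(1 + 4/(n0·0.15))]² = 159.8, so 160 per arm. This matches the plan exactly. The SAP's control rate ("Continuous abstinence rates at 52 weeks in clinical trials of varenicline were 22.5% for varenicline and 8.3% for placebo") gives 159 for 22.5% versus 37.5%. The sample size was therefore set for an unadjusted comparison of two proportions.

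**Step 2: power of the unadjusted test at 160 per arm, without continuity correction.**

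Φ[(0.15·√160 − 1.2762)/√0.4127] = Φ(0.967) = 83.3%, above the stated 80%.

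**Step 3: compare the two candidate tests by simulation.** From the documents: 160 per arm, overall rates held at 23% and 38% (23% in both arms under the null), two-sided 0.05. Assumed, because the documents give no figures: HSI scores 0 to 6 with probabilities 0.05, 0.08, 0.15, 0.25, 0.25, 0.14 and 0.08 (SD about 1.5), and the odds ratio for abstinence per HSI point shown in the first column. Each cell uses 10,000 trials and Wald tests, with HSI entered linearly in the adjusted model.

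| OR per HSI point (assumed) | Power, unadjusted | Power, adjusted | Tests disagree (planned effect) | Type I error if either may be reported | Conditional OR |
|---|---|---|---|---|---|
| 1.00 | 83.2% | 83.4% | 1.0% | 5.4% | 2.05 |
| 0.85 | 83.4% | 83.7% | 2.5% | 5.6% | 2.07 |
| 0.75 | 82.9% | 84.3% | 4.2% | 5.7% | 2.11 |
| 0.65 | 83.6% | 86.8% | 6.1% | 6.0% | 2.19 |
| 0.50 (extreme) | 83.3% | 89.8% | 8.9% | 6.2% | 2.42 |

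The Monte Carlo standard error is about 0.2 points for type I error (√(0.05·0.95/10,000) = 0.0022). Repeating the null runs with 40,000 trials each gave 5.1, 5.4, 5.7, 6.1 and 6.6% down the column. The first row is thus close to nominal, and the excess grows with the assumed HSI effect. Each test alone stays near 5%.

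The marginal odds ratio is (0.38/0.62)/(0.23/0.77) = 2.05 in every row. The conditional one rises to 2.19 at 0.65 per point and 2.42 at the extreme.

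**The case against.** The strongest defence is that the text describes the odds ratio column and the table note names the covariate for the adjusted column. The P-value column sits next to the unadjusted odds ratio, and Table 6 omits the HSI sentence, both of which fit that reading. Both estimates would be published and HSI is the only covariate named, which limits selective reporting. This is plausible, but the note says all analyses, and even on this reading no sentence assigns the P-value or calls either model primary. The ambiguity stands.

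It is also fair that the numerical consequence is modest. Both tests agree in more than 90% of simulated trials, and the type I error excess is about one point or less for odds ratios of 1.0 to 0.65. Marginal and conditional odds ratios side by side are acceptable if labelled. Naming the unadjusted model as primary would equally remove the contradiction and would match the sample-size basis.

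Two stronger readings are tempting and not supported:

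- **That an unadjusted primary test is underpowered.** A reader who simulates with the odds ratio of 2.05 fixed within HSI levels, 23% at the mean HSI, an SD of 1.4 and a log-odds slope of −0.6 per point will see unadjusted power of 75.4%. That set-up also shrinks the overall difference to 13.7 points (25.8% versus 39.5%), short of the planned 15. With 23% versus 38% held fixed, unadjusted power is about 83% in every scenario.
- **That the sponsor kept both options open after seeing results.** The SAP reports recruitment in the past tense, but nothing in it shows that outcomes had been examined.

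**Conclusion.** The contradiction is plain on the page and holds without any assumption: the SAP does not define a unique primary test. That alone warrants correction before the analysis is run.

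Its size rests on the assumed HSI distribution and HSI effect. For odds ratios of 1.0 to 0.65 per point, the two tests disagree in about 1 to 6% of trials at the planned effect, and reporting whichever is significant gives a type I error of about 5 to 6%, against the nominal 5%. At the extreme of 0.50 per point, disagreement is about 9% and type I error 6.2% to 6.6%.

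There is no shortfall against the stated 80% power. Adjusting would gain about 0 to 3 points over the moderate range and 6.5 points at the extreme, and nothing if HSI is not prognostic.

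**What to change.** In the SAP, delete the parenthetical word unadjusted from the model sentence and name one primary analysis: logistic regression of CO-verified continuous abstinence at 6 months on arm and baseline HSI score. This agrees with the SAP's own Table 2 note and uses a score already collected at baseline. Then:

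- state that HSI enters as a score, not as the Table 1 categories;
- take the Table 2 P-value and the headline confidence interval from this model, and say so in the column heading;
- label the unadjusted odds ratio as supportive;
- state that the GEE fallback carries the same HSI adjustment;
- label the Table 6 odds ratio as adjusted or unadjusted.

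Adding hospital as a covariate, or reporting a standardised risk difference to match the 15-point design target, is optional and not needed to resolve the contradiction. If the sponsor prefers the unadjusted model as primary, saying so and rewording the Table 2 note would also remove the ambiguity.

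The cost is a few sentences of SAP wording and the table headings. No new data are needed.
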